## Design

### Study setting and participants

The ECASeT trial (*Ensayo Clínico abierto y Aleatorizado para valorar la Seguridad de la Teleconsulta, frente a la consulta clínica presencial* in Spanish) is aimed at testing safety of remote consultations, based on its non-inferiority compared with face-to-face consultation. The ECASeT trial will be conducted in four centers in the healthcare area of *Alt Penedès-Garraf* in Catalonia (North-East Spain): three secondary hospitals (Hospital Sant Antoni Abat, Hospital Sant Camil, and Hospital Comarcal de l’Alt Penedès) and a rehabilitation center, all part of Healthcare Consortium Alt Penedès Garraf (CSAPG). All study sites belong to the public network of hospitals and primary care centers of the Catalan Health Service and provide universal healthcare to a catchment population of 247,357 inhabitants. Hospital departments from all areas (i.e., locomotive, internal medicine, surgery, gynecology, and pediatrics) are involved in the study.

Participants will be screened from all individuals, irrespective of age and sex, who require follow-up in outpatient consultations of any of the departments involved in the study. Eligibility criteria have been established based on the local guidelines for screening patients for remote consultation [15]. Briefly, to be eligible for remote consultation, patients have to have adequate digital literacy at the physician discretion and technological capacity to use the video conferencing software and undergo a type of follow-up that, due to the moderate complexity of the pathology, does not require physical examinations. Patients followed up in more than three departments, those with visual or hearing impairments that may hamper patient-physician communication, and those enrolled in another clinical trial that requires an experimental intervention during the follow-up will be excluded from the study.

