**Primary outcome**			
Rate of complications^b^ of the baseline disease	A secondary disease, an accident, or a negative reaction (including adverse reactions to treatment) occurring during the course of the baseline disease and usually aggravating the illness.	Measure: events, as recorded in the eCRF. Metrics and aggregation: event rate (i.e., proportion of patients experiencing an event within each arm and the follow-up period).	Investigator-reported in the eCRF Local EHR.

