**Secondary outcomes**			
Rate of severe complications of the baseline illness	A complication with significant impact on patient’s life and/or that require intervention by a healthcare professional	Measure: events, as recorded in the eCRF. Metrics and aggregation: event rate (i.e., proportion of patients experiencing an event within each arm and the follow-up period).	Investigator-reported in the eCRF Local EHR.
Rate of severe adverse reactions related to the treatment of the baseline condition	An undesired health event related to a drug administered to treat the baseline health condition	Measure: events, as recorded in the eCRF. Metrics and aggregation: event rate (i.e., proportion of patients experiencing an event within each arm and the follow-up period).	Investigator-reported in the eCRF
Rate of preventable hospitalizations	Hospitalizations due to illnesses secondary to the chronic diseases that can be managed in the outpatient setting^c^	Measure: events, as recorded in the eCRF. Metrics and aggregation: event rate (i.e., proportion of patients experiencing an event within each arm and the follow-up period).	Local EHR
Non-scheduled medical encounters related to poor control of the baseline disease	The following events will be considered: • Non-scheduled appointments (phone, videoconference, or face-to-face). • Visits to primary care services. • Visits to the emergency room. • Hospital admissions.	Measure: events, as recorded in the eCRF. Metrics and aggregation: event rate (i.e., proportion of patients experiencing an event within each arm and the follow-up period).	Investigator-reported in the eCRF Local EHR
Pharmaceutical prescriptions	The number of new prescriptions and renewals will be collected, along with the type of pharmaceutical prescription: long-term, acute process, or pro re nata.	Measure: ATC groups prescribed Metrics and aggregation: difference in number of ATC groups between baseline and last visit; the outcome will be measured as the mean and standard deviation, and median and interquartile range (i.e., 25^th^ and 75^th^ percentiles).	Administrative records.

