Usability	Usability parameters will be collected using two approaches: • Computer System Usability Questionnaire. • Technical incidents reported by the investigators.	Measure: Questionnaire score and number of technical incidents. Metrics and aggregation: score, expressed as the mean and standard deviation, and median and interquartile range (i.e., 25^th^ and 75^th^ percentiles). Cumulative number of incidents.	Phone call administration by trained interviewers to 10% of the study sample. Investigator report to the eCRF.
Satisfaction	Satisfaction survey CSAPG included in the satisfaction survey plan of the Catalan Health System.	Measure: Questionnaire score. Metrics and aggregation: score, expressed as the mean and standard deviation, and median and interquartile range (i.e., 25th and 75th percentiles).	Phone call administration by trained interviewers to 10% of the study sample.
Care provision expenditure	Expenses related to each of the interventions.	Measure: cost in euros of the year. Metrics and aggregation: mean and standard deviation per patient.	Administrative records.

*EHR* electronic health record

^a^In outcomes gathered from more than one data source, discrepancies or inconsistencies between data sources will be addressed by the scientific committee before the closure of the database

^b^The severity of complications and adverse events will be recorded using a scale with four categories: (a) MILD: does not limit activity and does not require medical follow-up; (b) MODERATE: mild-to-moderate impact on activity or requires minimal medical intervention or monitoring; (c) SEVERE: significant impact on activity or requires medical care; (d) VERY SEVERE: life-threatening or results in major disability or significant incapacity for the subject

^c^The list of conditions considered has been retrieved from ambulatory care sensitive conditions and include ICD-10 categories related to ischemic heart (I20, I240, I248, I249), asthma (J45, J46), COPD (J20, J41, J42, J43, J44, J47), heart failure (I110, I50, J81), seizures (G40, G41, R56, O15), diabetes (E100-E108, E110-E118, E120-E128, E130-E138, E140-E148), hypertension (I10, I119), and iron-deficiency anemia (D501, D508, D509)

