## Discussion

In this article, we describe the key elements of the design of an RCT to assess the safety of two modalities of synchronous remote consultations: video consultation and teleconsultation. Trials investigating the benefits and—less frequently—risks of remote consultation typically focused on a specific clinical condition [30–32]. Alternatively, we seek to address whether remote consultations can be considered overall safe in clinical conditions commonly followed up in a secondary hospital. While broadening the scope of the research, this approach raises notable challenges regarding the study design that are worth being discussed.

One of these challenges is the selection of the appropriate study outcome. Unlike the assessment of safety in drug therapy, commonly based on the number of adverse events related to the given drug, care delivery through remote consultation modalities lacks specific pre-defined harms that can be monitored. In the context of a particular diagnostic, the safety of a follow-up could be understood as the capacity of the care pathway to prevent an unexpected worsening of the disease (e.g., asthma exacerbations or cardiac arrest events). However, in our study, which encompasses many chronic conditions, the definition of the safety outcome had to include any possible complication that can be attributed to inadequate control of the baseline condition. We considered that listing all potential complications associated with the baseline conditions allowed in the trial would hamper excessively the study conduct and constrain the repertoire of possible complications. Instead, we chose a broad definition of complication [33]. To prevent unnoticed complications, we will complement the investigator’s assessment with a systematic screening of all events recorded in the EHR within the follow-up period, which are likely to include complications not recorded in the eCRF, such as visits to the emergency room, and primary care services related to the baseline condition.

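### The severe-adverse-reaction outcome is titled for treatment but defined for drugs only, and it is the only clinical-event row in Table 1 with no record-based source

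*Protocol article*

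**What the plan says.** All of the wording at issue is in the Protocol article, mostly in Table 1.

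- **Primary outcome row.** A complication includes "a negative reaction (including adverse reactions to treatment) occurring during the course of the baseline disease". The sources are "Investigator-reported in the eCRF Local EHR".
- **Severe-complications row (secondary).** It covers complications that have a significant impact on the patient's life or need a healthcare professional to intervene. It has the same two sources.
- **Severe-adverse-reaction row (secondary).** The title is "Rate of severe adverse reactions related to the treatment of the baseline condition", the definition is "An undesired health event related to a drug administered to treat the baseline health condition", and the only source is "Investigator-reported in the eCRF".
- **Table footnote a.** "In outcomes gathered from more than one data source, discrepancies or inconsistencies between data sources will be addressed by the scientific committee".
- **Discussion.** The investigator's assessment is to be supplemented by "a systematic screening of all events recorded in the EHR within the follow-up period", so that complications do not go unnoticed. The authors expect this screen to turn up events missing from the eCRF.
- **Study setting and participants.** The departments are "locomotive, internal medicine, surgery, gynecology, and pediatrics", and one of the four sites is a rehabilitation center.

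**The concern.** There are two separate problems in one row.

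**Scope.** The title speaks of treatment and the definition of a drug. In surgery, gynecology, locomotive departments and rehabilitation, treatment of the baseline disease is often not a drug. Two assessors faced with a severe reaction to a procedure could classify it differently, one going by the title and the other by the definition.

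**Source.** The row relies on one reporter, with no check against records. The trial is open by its name, and the section on screening, allocation and blinding blinds only the statisticians, so the reporting physician knows the arm. That physician also hears of reactions partly through the consultation itself, which is what the trial compares. If physicians hear of a different share of reactions in the two arms, the observed rates will differ for that reason alone. In a trial about safety, the concern is that fewer are heard of remotely, which would make remote care look better on this outcome than it is.

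**Working it through.** The plan gives no figure for this outcome, so there is nothing to reproduce. The check is a comparison of rows, followed by an illustration on assumed values.

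**1. Sources of the five clinical-event rows in Table 1**

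| Row | Investigator report in eCRF | Local EHR |
|---|---|---|
| Complications (primary) | yes | yes |
| Severe complications | yes | yes |
| Severe adverse reactions | yes | **no** |
| Preventable hospitalizations | no | yes |
| Non-scheduled encounters | yes | yes |

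Only the severe-adverse-reaction row has no record-based source.

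**2. Which column governs.** The measure column refers to events recorded in the eCRF in all five rows. That includes preventable hospitalizations, whose only source is the EHR. The phrase therefore cannot be meant to shut out EHR events, and the data-source column has to be read as the operative one.

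**3. One event followed through the table.** Take a severe drug reaction treated in the emergency room, found by the EHR screen and never entered by the investigator.

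- Primary outcome: it can count, because adverse reactions to treatment are included and the EHR is a source.
- Severe complications: it can count, because a professional intervened and the EHR is a source.
- Severe adverse reactions: it has no written route in. Footnote a reconciles sources only for outcomes that have more than one, and this row has one.

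If the investigator later learns of the event and enters it, it counts in all three.

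**4. A severe reaction to surgery or rehabilitation.** It falls under the row's title but outside its definition. The documents do not say which prevails.

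**5. Illustration of the source effect.** All inputs are assumptions. Let p be the true rate, s the share of reactions the investigator learns of, and e the share of the remainder that the EHR finds.

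Observed rate = p × [s + (1 − s) × e]

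Take p = 2% face-to-face and 3% remote (true difference 1.0 point), with e = 0 for the row as written and e = 0.8 with the EHR added.

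| s, face-to-face / remote | As written | With EHR |
|---|---|---|
| 0.9 / 0.6 | 1.8% v 1.8%, difference 0.0 | 1.96% v 2.76%, difference 0.80 |
| 0.9 / 0.7 | 1.8% v 2.1%, difference 0.3 | 1.96% v 2.82%, difference 0.86 |
| 0.9 / 0.9 | 1.8% v 2.7%, difference 0.9 | 1.96% v 2.94%, difference 0.98 |

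For example, 3% × [0.6 + 0.4 × 0.8] = 3% × 0.92 = 2.76%. The last line shows that with equal awareness the single source costs only a modest under-count. The distortion in the first two lines comes from the assumed gap in awareness. The 0.0 in the first line follows from the chosen inputs and is not a prediction.

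**The case against.** The strongest defense is that the single source may be deliberate. The Data sources section restricts the eCRF to variables that records cannot supply accurately, and attributing an event to a particular drug is a clinical judgment. But that section does not name this outcome. The primary and severe-complications rows also include treatment reactions and also require relatedness to be judged, yet they use the EHR. The article gives no reason for treating this row differently.

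Several other points on that side stand:

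- A secondary outcome narrower than the primary is not an error in itself. The fault is that the title does not say it is narrower.
- A reader might infer that EHR-detected reactions can never count here. That goes too far: only those the investigator does not also enter are lost.
- A reader might infer that procedural and rehabilitation reactions are definitely excluded. That assumes the definition overrides the title, which the documents do not state.
- A reader might infer that the outcome is biased toward remote care. The documents do not establish this. Eligible patients need no physical examination in follow-up and can report reactions by phone or video, so unequal awareness is possible but not shown.
- An unblinded reporter is not peculiar to this row. What is peculiar is the absence of a second source beside that reporter.

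The article condenses a fuller protocol, which may give operational detail. That does not remove a mismatch between title and definition, or a difference in source, that the article itself states.

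**Conclusion.** The point holds in limited form. The row's title and definition disagree on scope, and the row alone among the clinical-event outcomes lacks a record-based source although an EHR screen is already planned. Both follow from Table 1 as printed. The resulting rate may be under-ascertained, and possibly unequally by arm. The size is unknown, and the illustrative figures show a mechanism only.

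A reader might conclude that a severe safety signal is lost or that the non-inferiority result is compromised. Neither follows. Severe reactions, including those found only in the EHR, can still be counted as complications and as severe complications, and the primary analysis does not use this row. The consequence is confined to a secondary outcome whose reported rate may not mean what its title says. It should be corrected.

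**What to change.** Two changes to the severe-adverse-reaction row of Table 1:

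1. **Source.** List both investigator report in the eCRF and the local EHR, as in the primary row, and apply the EHR screen already planned and the reconciliation in footnote a. If the single source is intended, state why.
2. **Scope.** Make title and definition agree. Either widen the definition to undesired events related to any treatment of the baseline condition, or keep the definition and retitle the row as severe adverse drug reactions. Either resolves the mismatch. The first matches the scope of the primary outcome, while the second keeps the row distinct from severe complications.

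The cost is wording in one table row. No new data collection is needed, since the screen covers all recorded events. The added work is judging whether EHR events are related to treatment, a judgment of the kind the complication rows already require. Since the statistical analysis plan is to be written before the database is closed, it should carry the same wording.

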### Participant timeline

Figure 1 summarizes the participant timeline. All participants, irrespective of the study arm, will be scheduled follow-up visits at a frequency determined by the physician based on the diagnostic and therapy of the baseline disease and will receive a reminder (either SMS or phone call) before each visit. Physicians can schedule and cancel appointments at their discretion. At least three visits should be scheduled in the study setting: the baseline visit (i.e., screening visit), intermediate visits (pre-defined by the physician based on the follow-up needed for managing the baseline condition), and the final visit (i.e., either the follow-up visit closest to 12 ± 2 months after enrollment or before in case of discharge or early discontinuation).

**Fig. 1 Fig1:**
[figure not shown]
Participant timeline ^a^The frequency of the follow-up visits will be determined by the physician based on the diagnostic and therapy of the baseline disease and will receive a reminder (either SMS or phone call) before each visit. ^b^Either the follow-up visit closest to 12 ± 2 months after enrollment or before in case of discharge or early discontinuation

In addition to voluntary withdrawal, the following situations will lead participants in the remote consultation arms to discontinue the study: a change in their clinical status that requires face-to-face consultation and not following the procedures for remote consultation adequately. Patients allocated in the face-to-face arm will discontinue in case their health status discourages moving to the hospital for follow-up visits. The reasons for ending the study will be recorded in the eCRF.

The study will be temporarily interrupted if the local authorities or healthcare center managers decide to ban or limit face-to-face consultations because of the rapid spread of an infectious agent. This interruption can be partial in case banning face-to-face consultations does not affect all hospital services. The study will resume when face-to-face consultations are restored, and there is enough healthcare activity for adequate recruitment in all study arms. In case of a temporal interruption, the study will be automatically extended for a time that is at least equivalent to the interruption time.

The independent ethics committee can interrupt the study at any time in the advent of risk for participants, and the study sponsor can do it as well because of financial issues.

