Non-scheduled visits will be defined as any contact between the patient and the physician that occurs before the date established in the previous follow-up visit. Non-scheduled visits will be performed according to the study arm and type of remote consultation (i.e., phone or video) in which the patient has been allocated and will be considered for the analysis.

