The follow-up period planned by the investigator for the baseline disease will be retrieved from the local EHR. Other variables collected from EHRs at baseline will include sex, age, area of residence, the number of active prescriptions at the end of the screening visit, and the comorbidity burden, summarized using the Adjusted Morbidity Groups (AMG). Briefly, the AMG is a case-mix tool that generates a summary index of health risk by considering all chronic conditions and recent acute diagnostic codes [17]. The tool allows stratifying patients into mutually exclusive health-risk groups and has shown a high predictive capacity of healthcare and resource use outcomes, including mortality, hospitalization, visits to primary care, polypharmacy, and overall expenditure [18, 19].

For homogeneity regarding the rate of preventable hospitalizations, we considered all hospitalizations due to any of the ICD-10 diagnostic codes listed as ambulatory care sensitive conditions [20] managed in the participating departments, including conditions related to ischemic heart disease (I20, I240, I248, I249), asthma (J45, J46), chronic obstructive pulmonary disease (COPD) (J20, J41, J42, J43, J44, J47), heart failure (I110, I50, J81), seizures (G40, G41, R56, O15), diabetes (E100-E108, E110-E118, E120-E128, E130-E138, E140-E148), high blood pressure (I10, I119), and iron-deficiency anemia (D501, D508, D509).

Usability will be assessed by passive and active surveillance. Study investigators will record non-attendances, as well as all technical incidences that occurred during the visit in an unstructured field of the eCRF. For active surveillance, a trained interview panel will contact by phone a subset of 100 participants randomly selected from all patients who have completed the final visit. Interviewers will administer the computer system usability questionnaire (CSUQ), a validated questionnaire aimed at measuring the users’ satisfaction with the usability of computer systems in scenario-based usability studies [21].

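### A clinical change that calls for in-person care takes a remote patient out of the study, so later non-scheduled encounters probably go uncounted, with no matching trigger in controls

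*Protocol article*

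**What the plan says.** Four statements in the protocol article bear on this outcome.

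- **Discontinuation, remote arm** (Participant timeline, text after Fig. 1). Certain situations "will lead participants in the remote consultation arms to discontinue the study: a change in their clinical status that requires face-to-face consultation". What ends is participation in the study, not only the remote modality.
- **Discontinuation, control arm** (same place). "Patients allocated in the face-to-face arm will discontinue in case their health status discourages moving to the hospital for follow-up visits". Apart from voluntary withdrawal, this is the only rule given for controls.
- **End of follow-up** (Participant timeline). The final visit is the one closest to 12 ± 2 "months after enrollment or before in case of discharge or early discontinuation".
- **Outcome** (Table 1). Non-scheduled encounters linked to poor control of the baseline disease comprise unplanned appointments in any modality, primary care visits, emergency visits and admissions. The metric is the "proportion of patients experiencing an event within each arm and the follow-up period". The sources are the eCRF and the local EHR.

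Two further statements limit the point. The Interventions section says that unplanned visits follow the arm and modality "in which the patient has been allocated and will be considered for the analysis", so they count. The text under Outcomes and variables, after Table 1, adds: "The follow-up period planned by the investigator for the baseline disease will be retrieved from the local EHR".

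**The concern.** This secondary outcome is meant to show whether a mode of follow-up leaves the disease poorly controlled. In the remote arm, the event that ends participation is itself a clinical change, usually for the worse. If the counting window closes at that moment, observation stops in patients who may be about to need emergency care or admission. A control whose disease worsens and who attends in person unplanned has a counted event and stays under observation.

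Follow-up would then be cut short for reasons related to the outcome, and by a trigger that exists in one arm only. Because the metric is a simple proportion with no person-time, a remote patient who leaves without a counted event stays in an all-randomised denominator as a non-event. The Data management and analysis section says missing data will not be imputed, so nothing corrects for this later. The Discussion expects frequent arm switching because of care needs, but treats it only as a threat to power.

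**Working it through.** **Does the window close at the switch?**
1. Clinical change requiring in-person care leads to discontinuation of the study (Participant timeline).
2. Discontinuation brings the final visit forward (same section).
3. Events count within the follow-up period (Table 1).
4. No statement provides for counting after discontinuation, and none makes the planned period the counting window.

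Steps 1 to 3 together imply closure at the switch. This is an inference.

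**Who is affected?** The outcome is binary per patient. If the visit that triggers the switch was unplanned, it counts and nothing more can be lost for that patient. The loss falls on remote patients with no earlier counted encounter, for example when the need for examination emerges at a scheduled remote visit and the first emergency visit, primary care visit or admission comes later.

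**Size.** The plan gives no event rate or switch rate for this outcome, so there is no figure to reproduce. Assumed inputs:
- annual incidence p = 10% (borrowed from the control rate expected for the primary endpoint);
- switch at month 6;
- d = 2% to 10% of remote patients switched with no earlier counted encounter;
- later hazard k = 1 or 2 times baseline;
- analysis of all randomised patients.

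The loss in the remote proportion is d × q. Here q is the chance of a first encounter in the remaining half year: q = 1 − (1 − p)^(k/2).

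| k | q | d = 2% | d = 10% |
|---|---|---|---|
| 1 | 1 − 0.9^0.5 = 5.13% | 0.10 points | 0.51 points |
| 2 | 1 − 0.9 = 10.0% | 0.20 points | 1.0 points |

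**Larger values.** A loss of 4.0 points needs d = 10% and q = 40% together. At p = 10%, q = 40% after a month-6 switch implies a hazard of ln(0.6) / (0.5 × ln(0.9)) = 9.7 times baseline; q = 20% implies ln(0.8) / (0.5 × ln(0.9)) = 4.2 times. A higher underlying rate also raises q: with p = 30% and k = 1, q = 1 − 0.7^0.5 = 16.3%, and d = 10% gives 1.6 points.

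**Offset from controls.** If a share c of controls discontinues under the travel rule with the same later risk, the net bias is (d − c) × q. With k = 1:
- d = 10%, c = 1%: 9% × 5.13% = 0.46 points in favour of remote care;
- d = 2%, c = 2%: zero;
- d = 2%, c = 3%: −0.05 points, so the direction reverses.

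If encounters are counted to the end of planned follow-up in everyone, the loss is zero in both arms.

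**The case against.** The strongest objection is that the defect is inferred. The Participant timeline section dates the final visit; it does not say that ascertainment ends there. The planned follow-up period is to be retrieved from the EHR, and if Table 1 meant that period the loss would disappear. That reading is possible, but the text lists the planned period beside baseline variables and never makes it the counting window, while the rule that moves the final visit points the other way. The discontinuation rule is also stated, so this is more than a detail left to a fuller document.

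A second objection is that the data will exist anyway. Hospital records and the CHSS capture emergency visits, primary care visits and admissions whether or not the patient is still in the study, and all registries are to be linked. This stands. The analysis plan, to be written after the last final visit, could still extend the extraction. It would not supply encounters that only an investigator would have entered in the eCRF, though hospital records should hold most care given in the centres. The objection makes the problem easy to cure; it does not show that the plan cures it.

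Third, the affected group is narrow and the direction is not certain. Controls too ill to travel may themselves be at high risk. Both points stand and are built into the working.

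A reader might infer three stronger things that the documents do not support:
- **That the triggering visit itself is lost.** Table 1 includes face-to-face appointments, and the Interventions section says unplanned visits are considered.
- **That the Discussion limits this outcome to the follow-up period** by its "systematic screening of all events recorded in the EHR within the follow-up period". That sentence is about catching unnoticed complications; it does not set the window for non-scheduled encounters.
- **That affected patients are removed altogether through the per-protocol set.** The plan assigns that set to the primary analysis and names no analysis set for this outcome.

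**Conclusion.** The point holds as a cheap improvement to one secondary safety outcome. Followed as written, the rules take a remote patient out of the study on clinical change and, on the most natural reading, stop the count of non-scheduled encounters there. An unplanned in-person visit has no such effect in a control. The bias probably favours remote care, but discontinuations under the travel rule could cancel or reverse it.

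Its size cannot be derived from the documents. Under the assumed inputs it is about 0.1 to 1.0 percentage points before any control offset; larger values need a much higher later risk than a 10% annual rate implies. The conclusion rests on reading the follow-up period as ending at discontinuation and on analysing all randomised patients.

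**What to change.** 1. State that a switch to face-to-face care ends the allocated modality but not outcome collection.
2. Define the window for non-scheduled encounters as planned follow-up (12 ± 2 months, or discharge) in both arms.
3. Collect encounters to that point from the linked EHR and CHSS records for all randomised patients, including controls discontinued under the travel rule, unless consent to record access is withdrawn.

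The cost is low: two sentences and some extra record extraction. The registries are already to be linked and the planned follow-up period is already to be retrieved. The downside is that encounters after a switch are attributed to the remote arm although the patient is by then seen in person, which may dilute a difference between modalities.
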